### Second component: training and activities in PE classes

We conducted a four-hour training tailored to PE teachers at the beginning of the school semester. They were instructed to structure predominantly active PE classes, even in classes with a theoretical content. For example, a class focused on PA types and the relation between PA and a healthy diet would be structured in active lessons. We chose this because the active time in PE classes can be a beneficial factor to total PA and adolescent health [12, 20].

A supplemental manual with lesson plans and handouts was also developed and distributed to teachers. This manual was built for the program staff and was organized by grades (Grades 7–9). Materials from the *Educação Física* + Project [33], the PE-specific National Curriculum Standards [26], and health issues (www.bvsms.saude.gov.br) underpinned the manual’s content. The manual included four units: (i) PA and health (e.g., PA and leisure, cooperative games, PA with parents); (ii) health factors (e.g., sedentary time, diabetes and hypertension, quality of life); (iii) sports (e.g., athletics, volleyball, functional training, combat sports); and (iv) popular games (e.g., games, dancing and adventure sports). The adolescents’ production of posters and text with health issues content was completed either as classwork or as homework.

An undergraduate PE student supported all PE classes (20 classes with two PE lessons each week) during the semester. These staff collaborated in the planning of activities, material procurement and implementation of lessons. Additionally, one PE-related event (e.g., dance festival or games competition) was organized in order to combine PE classes and school cultural events (e.g., Student’s Week) and to encourage the active participation of students during school events.

### Third component: active opportunities in the school environment

These intervention strategies aimed to promote opportunities for PA practice within the school and to encourage it during out-of-school time, as well as to disseminate information on the importance of an active and healthy lifestyle [10, 11, 20]. Supervised and unsupervised activities were considered [11, 14]. Some of these strategies were focused on the engagement of girls — a high-risk subgroup for inactive lifestyles [6, 8].

Supervised 10–15 min sessions, called “Gym in School”, were performed twice a week. These sessions were composed of physical (e.g., stretching, located exercises) or dynamic (e.g., games and rhythmic activities) activities in small and large groups in order to involve young people in PA during free-time at school. A member of staff conducted these sessions in a variety of open spaces in the school (e.g., school entrance, courtyard, court).

Space and equipment were structured and made available to play games in free-time during the school day. Games were created by the program team based on the purpose of the intervention [10, 14, 20], and were tailored to the school environment and the PA interests of the young people (as identified in the pilot study). In each school, two small courts were painted on the school courtyard to be used for different games (e.g., foot- /volleyball and other popular games). Additionally, markings were made in the school gymnasium for use in games with several groups of students at the same time. A game called “Squash for Health” was created with positive and negative pictures of PA and screen time (e.g., cycling or watching television). During this game, points were gained on positive images and lost on negative images. A game called “Active Board” was set on a school wall because this game needs to be played on foot (i.e., to reduce the sitting time) during breaks. In groups of 4 to 6 participants, students threw a large die and would have to perform the corresponding activities indicated on the board (e.g., spend 20 s jumping on one leg) to complete the game.

An inventory of sports equipment (balls, rackets, nets, etc.) at each school was undertaken and the school coordinator was consulted about enabling students to have access to the equipment during their free-time at school. The school coordinators also released some PA equipment for the students’ use during school breaks. A control sheet was used to record the equipment used by the students.

Staff implemented these strategies in the first two weeks of the semester in order to guide the execution, access to facilities, and understanding of the rules of the games. During the semester, some PE classes and Gym in School sessions incorporated these games in order to encourage students to play them during free-time at school. Explanatory banners were displayed in schools explaining game rules and access to equipment. Motivational messages, for example, “Let’s play with friends!” and health messages, for example, “Practicing PA with friends is very good for the health!”, were also included on the banners.

### Fourth component: health education in the school community

Some of the previous strategies had an additional focus on promoting awareness about the benefits of an active and healthy lifestyle; principally, the materials produced in the classroom in general and PE classes and the banners exposed in schools (see Table 1).

Additionally, pamphlets with messages about active and healthy lifestyle were distributed in intervention schools. The program team designed these pamphlets based on other program materials (e.g., www.movebrasil.org.br, www.nchealthyschools.org; www.take10.net; www.letsmoveschools.org). The content was adapted to the program objectives and local circumstances. Teachers and professionals specializing in health education for young people selected the content and format of the health messages. Following this, marketing experts from the Municipal Education Department designed and produced the pamphlets.

Three pamphlets were directed at students: (i) PA and health; (ii) screen time and health; and (iii) healthy eating and healthy behaviors. Two pamphlets were directed at parents: (i) PA and parents/the family; and (ii) screen time and parents/the family. In each pamphlet, messages were also directed at intrapersonal (e.g., knowledge, self-assessment), interpersonal (e.g., social and family support), and environmental (e.g., supportive environments for healthy habits) factors (see Table 1).

The pamphlets were delivered during the first month of the program to a member of the school administration (coordinator or director). Guidelines were provided on the objectives of the pamphlets and their distribution. In general, the pamphlets focused on students were delivered early in the school day or during classes. The pamphlets focused on parents were delivered during parents’/teachers’ meetings or during parental visits to school. Teachers were encouraged to use the pamphlets during lessons that involved health messages.

### Control schools

Schools from the control group underwent one semester with the regular and conventional activities of a full-time school. In general, the control schools had two weekly PE classes that included content and activities according to the perspective of their teachers. Conventional PSE also took place in these schools.

### Outcome measures and evaluations

#### Data collection

The initial data collection was carried out before the start of the intervention (during two weeks in July 2014). A further data collection that incorporated the intervention phase took place immediately after the semester (two weeks in November and December 2014). Data collection occurred over two or three days in each school in order to include eligible students. Evaluators who had previously been trained in theoretical explanations and practical simulations administered the questionnaires. Some evaluators knew which schools were in the intervention and control treatments because they were enrolled in the intervention implementation; training was focused on the standardization of data collection independent of the condition to which the schools had been assigned in the trial. The questionnaire was administered to students in the classroom, without the presence of teachers. During administration the evaluators provided instructions and read each question aloud. The students then answered the questions. Other evaluators helped the students to answer the questions. Health professionals (PE and nursing) took anthropometric measures (weight, height and waist circumference).

Instruments validated for, or adapted to Brazilian young people were used to measure the study variables. Reliability of the self-reported measures was evaluated using Kappa’s index for dichotomous variables (e.g., gender), intra-class correlation coefficient for ordinal variables (e.g., economic class), and Cronbach’s alpha for scales (e.g., attitude scales). These reliability measures were obtained using a sample (*n* = 194) of students who were not enrolled in the *Fortaleça sua Saúde* program (see measures in the Table 2).

### Primary variables

#### PA

A list of 24 types of PA validated for Brazilian adolescents [34] was used to measure PA practice. This instrument allows students to report the weekly frequency and the daily duration of each PA they perform in a typical week. Thus, the weekly PA volume and PA levels can be estimated [3]. The PA-related behavior change stage was also evaluated using a question proposed by Marcus et al. [31]. The preference for PA in leisure-time (e.g., sports, games, dance, etc.) and the mode of traveling to school (car, bus, bicycle, on foot) was evaluated [35, 36].

### Screen time

Screen time during leisure-time was assessed using four items. These questions were related to habitual use of each screen time behavior (watching television, using the computer/video games) on weekdays and weekend days separately. These items have been used to measure screen time among adolescents from several countries [6, 8] including Brazil [7, 36]. The behavior change stage to reduce screen time was also evaluated using the criterion of a behavior change stage of two hours daily [37]. Every student answered two questions on the behavior change stages for reducing television watching or computer/video game use [37].

### Intrapersonal, interpersonal and environmental variables associated with PA

A validated instrument for Brazilian adolescents [38] was used to measure intrapersonal, interpersonal and environmental variables related to PA practice. The validation process included item selection based on international instruments, translated and content validated by experts, as well as a study of test-retest application (factorial validity and reliability) [38].

The questionnaire consisted of five scales and responses were recorded on a four-point Likert scale for PA-related variables: attitude (5 items), expectations (10 items), self-efficacy (12 items), perceived neighborhood environment (16 items), parental (6 items), and friends’ support (6 items). The program was focused on the school environment and, therefore, we decided to include two other scales. A teacher’s support scale (6 items) was built considering the structure of the items on the parental and friends’ support scales [38]. A perceived school environment scale (6 items) was built on PA-related school aspects that were identified in a systematic review [39].

### Intrapersonal, interpersonal and environmental variables associated with screen time

A questionnaire was developed and validated in order to measure intrapersonal, interpersonal and environmental variables associated with screen time among adolescents. This instrument was based on the socioecological theory [5] and considered similar questionnaires [37, 40–43] and a systematic review [5] of the item selection. The selected items underwent a process of translation and back translation and adjustments for cross-cultural adaptation (local culture and terms). Subsequently, five researchers experienced in validation tools and screen time evaluated the questionnaire and indicated adaptations and other potentially relevant items. Finally, a test-retest study with an independent sample was performed.

The questionnaire included nine four-point Likert scales. Three intrapersonal (attitude [3 items], expectations [12 items] and self-efficacy [11 items]), three interpersonal (family and friends modeling [4 items], social support [4 items] and family norms [6 items]) and three environmental (family environment [8 items], school environment [4 items] and environmental characteristics [8 items]) variables were considered from this instrument.

### Secondary variables

Secondary variables were evaluated in order to identify the impact of the *Fortaleça sua Saúde* program on other health-related factors (e.g., nutritional status, health behaviors) and academic performance (Table 2).

Anthropometric assessments included the measurement of body weight (kg), height (cm), and waist circumference (cm), and the calculation of body mass index (weight [kg]/height^2^ [m^2^]). International standardization was considered [44].

Health perception and quality of life were measured using two items from the World Health Organization Quality of Life [45] instrument. The question, “How would you describe the level of stress in your life?” [36], was also applied to measure stress levels.

Body image was obtained by self-assessment on the nine-silhouettes scale proposed by Stunkard et al. [46]. Considering these silhouettes, three questions were asked about the perception of current physical appearance, healthy body image, and ideal body [46].

Eating habits were evaluated using three items related to healthy foods (fruit juice, fruit and vegetables) and three unhealthy foods (soft drinks, savory foods and sweets) in a typical week [7, 35, 36]. Two items on the frequency of tobacco and alcohol use in the month preceding the survey, and a question on condom use in the year preceding the survey were included [7].

Two items on habitual sleep duration and sleep quality were used [36]. Additionally, the evaluation of sleepiness (i.e., chances of dozing or sleeping) in eight students’ living situations (e.g., studying, talking, inactive commuting to school) was considered [47].

Academic performance (standardized tests and academic achievement) and school attendance were evaluated [48]. The notes and standardized scores of the students were obtained from the schools and organized by semester to indicate the pre-intervention period (the first semester of 2014) and during/post-intervention (the second semester of 2014).

### Subsample of obese adolescents

In order to meet one of the secondary objectives of the program, students who were obese [49] were included in a specific assessment for the subsample. The presence of depressive symptoms was evaluated using the scale proposed by Silveira and George [50]. Eating disorders were assessed using the Eating Attitudes Test (EAT-26), validated for Brazilian adolescents [51]. Finally, sleep quality was measured using the Pittsburgh Sleep Quality Index (PSQI) [52].

Obese adolescents wore ActiGraph GT1M accelerometers on the left wrist for seven consecutive days. Epochs of five-seconds were programmed. Procedures for data validation and cut-off points (in counts/min) to determine the time spent in sedentary, light, moderate, and vigorous activities were based on a previous publication [53].

### Control and descriptive variables

Potential confounders were measured and included in the data analyses (Table 2). Students’ occupational status (working; not working) was measured [36]. Economic class and parents’ schooling were evaluated with the questionnaire of the Brazilian Association of Research Companies [54]. This instrument groups subjects into economic classes (A1 [richest], A2, B1, B2, C1, C2, D, and E [poorest]) based on a score combining ownership of assets, parents’ schooling and number of employees in the household.

### Evaluation plan

Following recommendations for evaluation in PA interventions [32], the *Fortaleça sua Saúde* program evaluation was performed by members who were not enrolled in the program design and implementation. The evaluation team was followed by specialists with experience in health education and evaluation. The implementation process, program visibility, and interests of the school community (students, teachers and parents) before and after the program implementation were considered [32]. Initially, the opinions of teachers, students and coordinators on the importance, ideas and acceptance of the implementation of a health program at their school were collated. During the program, members of the evaluation team visited the schools in order to identify the implementation process of the strategies as well as to assess the program visibility in the school environment. Immediately after the program, teachers, students and coordinators reported satisfaction with the strategies and their continuity prospects for the following semesters. Six months after the program end (June 2015), the evaluation team will observe the continuity of intervention strategies. This data collection will involve independent samples and instruments in order to answer each evaluation aim.

An economic evaluation of the intervention was included in the evaluation plan. This incorporated the start-up and operational costs of the intervention delivery, both monetary and nonmonetary inputs. The intervention costs were assessed on the basis of the attendance lists, registration forms, and project logbooks of the researchers and school professionals.

### Statistical considerations

All sample size power calculations considered a statistical power of 80 % and a 5 % significance level for two-tailed tests. An odds ratio of two [35] was considered, that is, an odds ratio of two students from the intervention group becoming active after the program compared to their peers from the control group (www.openepi.com). Therefore, we estimated a sample of 480 subjects (1:1 between intervention and control groups). A cluster sample selection procedure can involve biases [35] and we, therefore, decided to duplicate the study sample for 960 schoolchildren. Additionally, considering a margin of 20 % for possible losses and refusals, ~1,200 students would be a sufficient sample size to detect a moderate-sized effect with 0.80 of power.

Moderate mediated effect sizes (structural equation models) of the intervention on the primary outcomes were expected (effect size of 0.30). We considered approximately 70 observed variables and the development of up to ten latent variables, considering the number of items included in the PA and screen time questionnaires. Thus, the recommended minimum sample size was 400 adolescents (www.danielsoper.com/statcal); a doubled sample due to the cluster sample selection procedure [35] and an anticipated 20 % dropout rate during the intervention estimating a sample of 960 students. Hence, ~1,200 students would be a sufficient sample size to detect a moderate-sized effect with 0.80 of power for the mediating variables.

We will test whether randomization resulted in a balanced distribution of variables between control vs. intervention students, as well as participating vs. dropout students. The variables that have differing distributions between the two groups will be entered as confounders in all models that test the effectiveness of the *Fortaleça sua Saúde* program.

The effect of the *Fortaleça sua Saúde* program on the primary variables will be tested in accordance with the intention-to-treat principle and in a completers-only framework using Mplus [55]. Intention-to-treat and completers-only analyses will be performed in order to identify the effect of the intervention condition in comparison to the control condition.

Because the data have a multilevel structure (i.e., individuals are clustered within a school), the individual respondents may not necessarily be independent within each school. To correct this, the procedure for complex samples in Mplus will be used in relation to the school. Finally, the results will be reported in accordance with the Consolidated Standards of Reporting Trials (CONSORT) [56].

Statistical procedures proposed by MacKinnon and Dwyer [57] will be considered to identify the effectiveness of the program according to the primary variables and mediating variables, as a common method of intervention study on PA and screen time [13, 15]. Initially, changes in the primary variable (e.g., changes in weekly PA time) will be considered in a regression under the influence of the independent variable (intervention group). In the second model, the mediating variables will also be included in the regression model. Thus, the value of the mediated effect will be calculated by the difference coefficient of the independent variable between the two models [57]. The measure of effect will be expressed in standardized scores (beta) or as an odds ratio, depending on the nature and manner of treatment of the primary variables.

Regression models will also be built in order to identify the effectiveness of the program on secondary variables (e.g., body image, eating habits). The effectiveness of the program on variables among obese students will be analyzed separately using the same statistical procedures. The implementation and economic evaluation will be qualitatively and quantitatively analyzed, considering the different indicators of the evaluation of PA interventions [32]. All analyses will be built using the Mplus program and will be adjusted for possible confounding variables (behaviors at baseline and control variables). The level of significance for the study will be 5 % for two-tailed tests.

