## Background

An active (i.e., regular physical activity [PA] as well as low levels of sedentary time) and healthy (i.e., attitudes positively associated with health, such as healthy eating habits) lifestyle can lead to many individual and collective benefits at any age [1–4]. However, a focus on the early years has been employed due to the potential present and future health impact on the population [1–5].

Although the benefits of active and healthy lifestyles are widely reported, few young people lead an active lifestyle. International data estimates that only two out of ten adolescents meet the PA recommendations (300 min or more of moderate to vigorous PA per week) [6]. In Brazil, the proportion of students who met this recommendation fell from 43.1 % in 2009 to 30.1 % in 2012 [7]. Additionally, other unhealthy lifestyle factors are common among young people (e.g., excessive screen time and inadequate eating) [6–8]. Thus, interventions focused on promoting active and healthy lifestyles in young people are a public health priority [3, 4, 9, 10].

Systematic reviews have summarized the evidence of interventions that aimed to promote PA [10–15] and reduce sedentary behavior [5, 10, 11, 15, 16] among young people. Important implications can be identified from these reviews. First, in general, interventions had modest effect on behavior change [10, 11, 14, 16]. Second, multicomponent programs (i.e., strategies focused on different settings and individuals from the school, the family and/or the community) had more promising results on the promotion of active lifestyles [5, 10–12]. Third, the school seems to be an appropriate setting for many of the intervention strategies [10–12, 15]. Finally, the effectiveness of programs on PA and on sedentary behavior-related variables (e.g., risks and benefits, self-efficacy, social support, environmental perceptions), and how these variables (i.e., mediating variables) explain active lifestyle changes among adolescents has been little explored [13, 15].

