The *Fortaleça sua Saúde* program was a cluster randomized controlled trial that had a sample size with sufficient statistical power to find the expected moderate effect [11, 16, 35] on the active lifestyle variables, as well as to identify the mediators of these behaviors. The inclusion of students in adolescence was also a strength of the study because similar analyses had only included children [17] and there is a worrying estimate of inactive and unhealthy lifestyles among adolescents [6, 8], including in Brazil [7]. Other strengths of this program were the measurement of potential mediators of PA and screen time [5, 13, 15, 16], and the analysis of whether PA and screen time were predictors of other health factors (e.g., diet and quality of life) and academic performance. A specific evaluation of obese students may indicate the health benefits of this program for a high-risk subgroup of biological, behavioral (objectively-measured), and psychological health problems [4]. Finally, the evaluation of the acceptance, implementation and maintenance of this program may indicate how the *Fortaleça sua Saúde* program strategies may be extended and adapted to the school context [4, 32].

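### The 0.80 power for an odds ratio of 2 leaves out the number of schools: on the plan's own figures, six schools give about 57% to 65%

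*Protocol article*

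**What the plan says.** The article describes a trial randomised by school. Setting and population gives six eligible schools, three per arm.

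Under Statistical considerations, "All sample size power calculations considered a statistical power of 80 % and a 5 % significance level for two-tailed tests". On the effect, "An odds ratio of two [35] was considered", for students becoming active. This gives 480 students, 1:1. Because cluster selection can introduce bias, the authors write "we, therefore, decided to duplicate the study sample for 960 schoolchildren". The last step is "considering a margin of 20 % for possible losses and refusals, ~1,200 students would be a sufficient sample size", and the power claimed for that sample is 0.80.

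The Discussion lists this among the study's strengths: the trial "had a sample size with sufficient statistical power to find the expected moderate effect".

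The section gives no school-level ICC, cluster size, number of schools or control proportion. The ICC values in Table 2 are reliability coefficients of the questionnaire items, not correlations within schools.

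**The concern.** Doubling for clustering amounts to assuming a design effect of 2. Whether that is enough depends on the ICC and on how many students each school contributes.

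A second loss is separate from the design effect. When schools are randomised, the treatment comparison has as many degrees of freedom as there are schools minus two, here four. A calculation made for individually randomised students and then multiplied by two takes no account of this.

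The stated power is presented as settled and as a strength. If it is too high, readers of a non-significant result would have reason to give it more weight as evidence against an effect than the design allows. The article says that the results are meant to inform public policy.

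**Working it through.** **Inputs.** From Statistical considerations: odds ratio 2, 80% power, two-sided 5%, 480 students, factor 2, 20% losses. From Setting and population: 3 + 3 schools. From Recruitment of schools and students: 1,085 students followed up. From Background: 30.1% of Brazilian students met the activity recommendation in 2012. The ICCs of 0.01, 0.02 and 0.05 used below are assumptions.

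**1. The plan's own chain.** 480 × 2 = 960, and 960 / 0.80 = 1,200. The arithmetic is right. The 480 itself needs a control proportion, which is not given. With the two-proportion formula without continuity correction, 480 arises at 12.3% (against 21.9% under an odds ratio of 2) and also at 78.1%. With continuity correction it arises at about 13.7% or 75.9%. At 30.1% the same formula needs only about 281 students.

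**2. The implied ICC.** Design effect = 1 + (m − 1) × ICC, where m is students per school. Setting it to 2 gives ICC = 1/(m − 1):

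- 960 students, m = 160: 1/159 = 0.0063
- 1,085 students, m = 180.8: 1/179.8 = 0.0056
- 1,200 students, m = 200: 1/199 = 0.0050

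**3. Power with six schools, granting that ICC.** At 960 students the effective sample is 960/2 = 480, so by the plan's own calculation the noncentrality is 1.960 + 0.842 = 2.80. For other sizes it is 2.80 × √(effective sample / 480). With 6 − 2 = 4 degrees of freedom the critical value is 2.78, not 1.96.

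| Students | Effective sample | Noncentrality | Power, normal reference | Power, t(4) |
|---|---|---|---|---|
| 960 | 480 | 2.80 | 80% | 56% |
| 1,085 | 542 | 2.98 | 85% | 61% |
| 1,200 | 600 | 3.13 | 88% | 65% |

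Working instead from 12.3% v 21.9% with unpooled variance gives a noncentrality of 2.82 at 960 and t(4) power of 57%; at 1,085 it gives 62%. The two routes agree to within a percentage point.

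**4. The cost of a normal reference.** If the statistic follows t(4), a cut-off of 1.96 has a two-sided error of about 12%, against the stated 5%.

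**5. The ICC that would give 80%.** Anchored on 480 students for 80% power, t(4) power reaches 80% only if the ICC is at most about 0.0007 at 960 students, 0.0014 at 1,085 or 0.0019 at 1,200.

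**6. Sensitivity at 1,085 students.** Noncentrality = (p1 − p0) / √[(p0q0 + p1q1) / (n per arm / design effect)], referred to t(4). A power of 80% needs a noncentrality of 3.76.

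| ICC | Power for odds ratio 2, control 12.3% | Detectable odds ratio at 80% | Power for odds ratio 2, control 30.1% | Detectable odds ratio at 80% |
|---|---|---|---|---|
| 0.0055 | 62% | 2.3 | 83% | 1.9 |
| 0.01 | 49% | 2.7 | 70% | 2.2 |
| 0.02 | 33% | 3.4 | 50% | 2.7 |
| 0.05 | 18% | 5.3 | 27% | 4.1 |

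**The case against.** The best defence is that the shortfall rests on things the article does not fix. At a control proportion of 30.1% and the implied ICC, power with 4 degrees of freedom is 83%. This stands as a limit on what can be claimed. It does not rescue the stated calculation, because at 30.1% the starting figure would be about 281 students, not 480.

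Second, the article specifies the complex-samples procedure in Mplus and names no t reference, and under a normal reference the plan's case does give 80%. That is so, but with six schools such a test would not hold the 5% level that the same section states. The two stated figures, 80% and 5%, cannot both hold on these inputs.

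Third, the models adjust for baseline behaviour, which could lower the residual ICC. This is fair and should be noted. The article claims no such gain, and at 1,085 students the ICC would have to fall to about 0.0014.

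A reader might also infer more than the article supports:

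- **That the trial had at best an even chance of detecting an odds ratio of 2.** At the implied ICC the figures run from 56% to 83%. Values at or below 50% need an assumed ICC of 0.01 or more.
- **That 480 fixes the control proportion at 12.3%.** Other values reproduce it (step 1).
- **That more students per school would be useless.** At 12.3% and ICC 0.0055, power rises from 59% at 960 to 75% at 2,400. Only above an ICC of 6/480 = 0.0125 can no number of students in six schools reach an effective sample of 480.
- **That screen time has no power figure at all.** The second calculation covers mediated effects on the primary outcomes and counts items from the screen-time questionnaire.
- **That the Background's "interventions had modest effect on behavior change" contradicts the moderate effect expected in the Discussion.** Neither term is quantified, and the Discussion also cites the source of the odds ratio of 2.

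**Conclusion.** The concern holds. The stated power omits the number of schools, and this can be shown from the plan's own figures without any outside ICC. Granting both the 480 and the doubling, a 3 v 3 comparison held to two-sided 5% has about 57% power at 960 students, 61% to 62% at 1,085 and about 65% at 1,200, against the stated 80%.

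This rests on t with 4 degrees of freedom as the reference for a comparison of six schools, and on equal school sizes. The trial's actual power remains unknown, because neither the school-level ICC nor the control proportion is given. Over the assumed range it runs from 18% to 83%. The supportable conclusion is therefore that 0.80 is not delivered by the calculation shown, not that the trial's power was any particular figure.

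**What to change.** 1. In Statistical considerations, withdraw or qualify the statement that "1,200 students would be a sufficient sample size to detect a moderate-sized effect with 0.80 of power". Say that the factor of 2 corresponds to an ICC of about 0.005 to 0.006 and that the number of schools was not used.
2. Replace it with power and detectable odds ratios for 3 v 3 schools with 4 degrees of freedom over a range of ICCs, as in the second table. State the control proportion for each scenario, mark the ICCs as assumptions, and note that baseline adjustment could lower the residual ICC.
3. In the Discussion, remove or qualify sufficient power as a strength.
4. State that a non-significant result will not be read as absence of effect.

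The cost is wording and one small table, and a published figure becomes less favourable. All six eligible schools were already in the trial and follow-up is complete, so no extra enrolment is proposed.
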